#### Exclusion criteria

Participants are excluded if any of the following apply:

Alternative diagnoses: (1) Suspected bacterial infection (e.g., tonsillar exudate, cervical lymphadenitis, or fever ≥39.5°C). (2) Herpangina, hand-foot-mouth disease, or other viral exanthems.

Comorbidities: (1) Chronic pharyngitis/tonsillitis (>3 episodes/year). (2) Immunodeficiency, asthma, or severe cardiopulmonary diseases.

Medication factors: (1) Allergy to XFOL components or control drug (e.g., Lianhua Qingwen granules). (2) Use of immunosuppressants or systemic corticosteroids within 4 weeks.

Logistical contraindications: (1) Participation in other clinical trials within 30 days (2) Inability to comply with protocol (e.g., language barriers, geographic instability).

#### Study discontinuation

Participants may discontinue the trial under the following conditions (documented in Case Report Form, CRF):

Voluntary withdrawal: The participant or their legal guardian chooses to withdraw from the study at any time.

Protocol violations: Incorrect enrollment (e.g., retrospective diagnosis of bacterial infection), or non-adherence to medication (>20% doses missed).

Safety-related termination: (1) Severe adverse events (SAEs) requiring hospitalization. (2) Disease progression necessitating rescue antibiotics.

Investigator decision: (1) Clinical judgment deems discontinuation in the participant’s best interest. (2) Discontinued participants receive appropriate medical management per hospital protocols.

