### Trial design

This trial employs a multi-center (three-centers), randomized, parallel-group, non-inferiority design. Eligible participants, after signing written informed consent, will be randomly assigned in an equal ratio to either the trial group or the control group. Enrolled participants will receive medication for a 5-day treatment duration. After completing 5 ± 1 day of continuous medication, participants will return to the hospital for follow-up, return the study medication and diary cards, and terminate treatment. The flowchart of the trial design is presented in Figure 1.

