#### Treatment course

The treatment duration is 5 days (±1 day) as this period covers the critical progression phase of the disease. Participants will return for follow-up visits after completing the course to return unused medications and logcards. A post-treatment telephone follow-up will be conducted 24 h after discontinuation to assess body temperature, concomitant medications, and adverse events.

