#### Rescue therapy

Acetaminophen oral suspension (brand name: Tylenol; 100 mL:3.2 g) will be administered as antipyretic rescue medication for participants with axillary temperature ≥38.2°C (Liu and Gu, 2017). For dosage, 1–3 years (12–15 kg): 3 mL per dose; 4–6 years (16–21 kg): 5 mL per dose; 7–9 years (22–27 kg): 8 mL per dose; 10–12 years (28–32 kg): 10 mL per dose. For frequency, repeat every 4–6 h if fever persists, with a maximum of 4 doses within 24 h. Persistent high fever unresponsive to rescue therapy requires immediate medical intervention.

During the trial, the use of antibiotics, antiviral agents, or other TCM with purported effectiveness for pediatric acute pharyngitis/tonsillitis is strictly prohibited. Additionally, non-protocol treatments such as infrared therapy, cupping, and acupuncture are disallowed throughout the study and follow-up periods. Acetaminophen is permitted for fever management (axillary temperature ≥38.2°C), and its dosage must adhere to the product instructions. All concomitant medications, including rescue therapies, must be meticulously documented in the CRF and original medical records, specifying the generic drug names, dosages, administration times, and reasons for use to ensure comprehensive data integrity and protocol adherence.

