#### Statistical analysis data set

Full Analysis Set (FAS): Includes all randomized participants who received at least one dose of the study drug and provided post-baseline effectiveness data. Missing primary outcomes are imputed using the last observation carried forward (LOCF) method under the intention-to-treat (ITT) principle. FAS serves as the primary population for effectiveness analyses.

Per-Protocol Set (PPS): A subset of FAS comprising participants with protocol adherence, complete baseline data, no major protocol deviations, and measurable primary endpoints. PPS is used for sensitivity analyses of primary outcomes.

Safety Set (SS): Encompasses all participants who received ≥1 dose and had safety assessments. Adverse event rates are calculated using SS.

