### Analysis of secondary outcomes

#### Time-to-event endpoints

For time to onset/resolution of sore throat (WBS or TCM-assessed) and complete fever resolution time, survival analyses will be conducted using Kaplan-Meier curves to estimate cumulative event probabilities, with between-group comparisons via log-rank tests. Results will be reported as median event times and adjusted hazard ratios (HR) derived from Cox proportional hazards models, accounting for baseline severity and age. Participants lost to follow-up will be censored at their last recorded observation.

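### A child who leaves the trial for progression needing antibiotics is not defined as a non-responder: LOCF can count that child as effective in the FAS, and the PPS would probably drop the child

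*Protocol article*

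**What the plan says.** All references are to the protocol article.

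- **Study discontinuation.** The list opens with "Participants may discontinue the trial under the following conditions". Under safety-related termination it includes "Disease progression necessitating rescue antibiotics". Under protocol violations it includes "non-adherence to medication (>20% doses missed").
- **Rescue therapy.** During the trial "the use of antibiotics, antiviral agents, or other TCM with purported effectiveness for pediatric acute pharyngitis/tonsillitis is strictly prohibited".
- **Primary outcomes.** Effective means a fall of at least 50% in WBS from baseline, and resolved means a score of 0, both at Day 5. Neither definition mentions antibiotics, progression or withdrawal.
- **Statistical analysis data set.** For the FAS, "Missing primary outcomes are imputed using the last observation carried forward (LOCF) method under the intention-to-treat (ITT) principle". The PPS is limited to adherent children without major deviations and with a measurable primary endpoint.
- **Missing values.** LOCF is described as giving a conservative estimate of treatment effects.
- **Analysis of primary outcome.** Both FAS and PPS must show non-inferiority (margin 10 points), on both primary endpoints.
- **Trial design.** "After completing 5 ± 1 day of continuous medication, participants will return to the hospital for follow-up, return the study medication and diary cards".
- **Treatment course.** "A post-treatment telephone follow-up will be conducted 24 h after discontinuation to assess body temperature, concomitant medications, and adverse events". WBS is not among the items asked.

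**The concern.** Progression to antibiotics is a treatment failure in any ordinary sense, yet the endpoint definition does not recognise it. If the child leaves and the diary stops, the stated rules look only at the last recorded WBS. A score that improved early, before the child worsened, can stand as the Day 5 result.

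The usual defence in a non-inferiority trial is to require agreement between FAS and PPS. Here the two sets can fail together: the FAS may relabel the failure as a success, and the PPS probably deletes it. If XFOL had more such failures than the control, both sets would understate its deficit, and an inferior treatment could pass. Calling LOCF conservative does not answer this, because shrinking a true deficit is the anti-conservative direction in a non-inferiority comparison.

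A separate, smaller gap concerns children who finish on Day 4. They are within the permitted 5 ± 1 days, but a Day 5 endpoint may have no Day 5 measurement.

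**Working it through.** **1. The plan's own figure.** Inputs from Sample size calculation: 0.9143 (XFOL), 0.7692 (control), Δ = 0.10, one-sided α = 0.025, power 80%.

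n = (1.960 + 0.842)² × [0.9143×0.0857 + 0.7692×0.2308] / (0.1451 + 0.10)² = 7.849 × 0.2559 / 0.0601 ≈ 33.4, so 34 per group, as stated. At 60 per group the same approximation gives power 0.96.

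**2. What the rules do to one child.** The scale has six faces from 0 to 10, hence steps of 2. From a baseline of 8 or 10, a last score of 4 already meets the 50% rule. Suppose a child goes from 8 to 4, then progresses, receives antibiotics and leaves:

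- FAS, effective rate: success by LOCF.
- FAS, resolution rate: failure, because 4 is not 0.
- PPS: probably excluded, as a prohibited drug was used and Day 5 was not measured.

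A false success on both endpoints requires a last score of 0.

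**3. Effect on false non-inferiority.** Assumptions, not in the article: true rates exactly at the margin (control 0.7692, XFOL 0.6692); 60 per group; shares d_T and d_C leave for progression and are all true failures; LOCF credits a fraction s of them. The article gives no expected effective rate, so 0.7692 stands in for either endpoint.

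- FAS difference = −0.10 + s(d_T − d_C)
- PPS difference = 0.6692/(1 − d_T) − 0.7692/(1 − d_C)
- P(non-inferior) = Φ[(difference + 0.10)/SE − 1.96], unpooled SE

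For d_T = 10%, d_C = 5%, s = 0.5:

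- FAS: 0.7192 − 0.7942 = −0.075; SE = √[(0.7192×0.2808 + 0.7942×0.2058)/60] = 0.0780; Φ(0.320 − 1.960) = 0.0505.
- PPS: 0.7436 − 0.8097 = −0.0661, with 54 and 57 children; SE = 0.0790; Φ(0.429 − 1.960) = 0.063.

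| Share leaving, XFOL / control | FAS, s = 0 | FAS, s = 0.25 | FAS, s = 0.5 | PPS |
|---|---|---|---|---|
| 10% / 10% | 0.025 | 0.025 | 0.025 | 0.018 |
| 10% / 5% | 0.025 | 0.036 | 0.051 | 0.063 |
| 15% / 5% | 0.025 | 0.050 | 0.095 | 0.169 |

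With equal shares of 5% to 20%, the FAS stays at 0.025 and the PPS falls to between 0.021 and 0.009. These are rates for one endpoint in one set. Since both sets must pass, the joint rate cannot exceed the smaller of the two.

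**4. Day 4 finishers.** Four days at four doses a day is 16 of 20, so exactly 20% missed, which is not more than 20%. They are completers. The diary goes back at the visit, and the call 24 h later falls on Day 4 + 1 = Day 5 but does not ask for WBS.

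**5. Power if failures are counted.** Multiply both design rates by (1 − d), with 60 per group. At d = 10%: 0.8229 against 0.6923, SE = 0.0773, Φ(0.2306/0.0773 − 1.96) = 0.85. At 5% it is 0.91, and at 20% it is 0.72.

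**The case against.** Several stronger readings are tempting, and the article does not support them.

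- **That every such child leaves automatically.** The text is permissive: the child may discontinue.
- **That missed doses or a Day 4 finish are hidden failures.** Missing more than 20% of doses is non-adherence, not necessarily failure. A Day 4 finisher has completed treatment within the window, and carrying a Day 4 score forward in a resolving illness would tend to understate success.
- **That both primary endpoints are corrupted in the FAS.** A child who stops at 4 remains unresolved. If no such child has a last score of 0, resolution in the FAS is counted correctly (s = 0 in the table). Because both endpoints must succeed, resolution can still block a false claim, though only if XFOL is also inferior on resolution. WBS is recorded daily, so worsening may also be captured before the child leaves.
- **That the bias always favours XFOL.** It does so only if these failures are commoner on XFOL, whereas the design expects XFOL to do better. An example in which the remaining children respond equally in both arms makes the PPS difference zero by construction and proves nothing about its likely size.
- **That the time-to-event analyses are informatively censored.** The rule reads "Participants lost to follow-up will be censored at their last recorded observation". Extending it to children withdrawn for progression is an inference, and it touches secondary endpoints only.

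It can also be said that such rules belong in an SAP, which is not shown, and that multiple imputation is planned as a sensitivity check. But the article does not leave the matter open: it fixes the endpoint on WBS alone and prescribes LOCF for missing values. Multiple imputation does not count these children as failures either. What stands of the objection narrows the point to antibiotic or progression withdrawals. It does not remove it.

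**Conclusion.** The point holds in this limited form. Under the stated rules, a child who progresses to antibiotics can be counted as effective in the FAS and would probably be absent from the PPS, so the two-set requirement does not reliably protect the conclusion. The description of LOCF as conservative is not justified for this comparison.

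The size depends on assumed shares. At 10% against 5%, with half credited, the error for one endpoint about doubles in the FAS and is about two and a half times nominal in the PPS. With no imbalance there is no inflation. The article allows for 20% dropout overall but says nothing about its causes or its split between arms, so the actual size cannot be known in advance.

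The missing Day 5 score for Day 4 finishers is a minor, separate measurement gap. Study discontinuation, Rescue therapy, Primary outcomes, Statistical analysis data set and Missing values need to be reconciled before unblinding.

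**What to change.** 1. In the primary FAS analysis, score any child who receives antibiotics for disease progression, or is withdrawn for it, as not effective and not resolved, in place of LOCF. Add a sensitivity analysis that retains these children in the PPS as non-responders. Making this the main PPS analysis would conflict with the set's own definition.
2. Separate stopping study drug from ending observation: continue the WBS logcard to Day 5 for children who stop, unless consent is withdrawn.
3. Add a WBS question to the existing 24-h call, to supply Day 5 for children who finish on Day 4.
4. Delete the statement that LOCF is conservative.

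The treatment-stopping rules stay as they are. The cost is protocol and SAP wording, a longer diary for some children and one telephone question, with no added visit. Response rates will be lower and some power is lost: from about 0.96 to 0.91 or 0.85 if 5% or 10% of children in both arms are counted as failures.

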#### Sample size calculation

Primary endpoints: throat pain resolution rate and overall effective rate

Parameters: Expected throat pain resolution rate: 91.43% (intervention group) vs. 76.92% (control group), non-inferiority margin (Δ) = 0.1 (Zhu et al., 2014), one-sided α = 0.025, power (1-β) = 80% (Chow et al., 2017). Initial calculation using PASS 15 software yielded 34 participants per group.

Adjustments:

A 20% dropout rate adjustment (n = 34/0.8 ≈ 43) required 44 participants per group (total 88).

To account for potential challenges in pediatric compliance and ensure robust statistical power, the final sample size was increased to 120 participants (60 per group). Since non-inferiority must be demonstrated for both primary endpoints to consider the trial successful, no adjustment for multiple testing is required in the analysis phase.

#### Randomization, allocation concealment, and blinding

This multicenter trial will employ a central block randomization method (block size = 4) to ensure balanced allocation between the two groups, each comprising 60 participants. An independent statistician from the Center for Evidence-Based Chinese Medicine, Beijing University of Chinese Medicine, will generate the randomization sequence using SAS software, with site-specific coding ranges assigned to each participating center. Sequentially numbered, sealed, opaque envelopes will be used to maintain allocation concealment. Medications will be pre-packaged by personnel uninvolved in trial execution and stored in hospital pharmacies to preserve blinding.

Trained site investigators will enroll eligible participants and obtain informed consent. Upon enrollment, a designated third-party staff member will dispense study medications labeled with unique identifiers corresponding to the randomization list. To maintain blinding, both the participants and investigators will be unaware of treatment assignments throughout the trial. Blinding will also extend to outcome assessors and data analysts to minimize evaluation bias. All site personnel will undergo standardized training to ensure adherence to the trial protocol.

### Intervention

#### Trial group

Intervention: Participants in the trial group will receive XFOL and a matching placebo for XYG (4 g/sachet). Both the active drug and placebo are indistinguishable in appearance, taste, and odor. For ages 3–6 years, 5–10 mL of XFOL (or placebo), administered orally 4 times daily; for ages 6–14 years, 7.5–15 mL of XFOL (or placebo), administered orally 4 times daily. The oral solution and placebo must be shaken thoroughly before use. The color, smell and taste of the placebo for XYG drug are consistent with those of XYG.

XFOL ingredients: *Lonicera japonica*, Forsythia suspensa, Isatis indigotica, Mentha haplocalyx, Bupleurum chinense, Lophatherum gracile, Arctium lappa, Platycodon grandiflorus, Scutellaria baicalensis, Gardenia jasminoides, Phragmites communis, CaSO_4_·2H_2_O, Schizonepeta tenuifolia, Saposhnikovia divaricata, Bombyx batryticatus, Glycyrrhiza uralensis, Massa Medicata Fermentata, Citrus reticulata, Cryptotympana atrata, Paeonia lactiflora, Prunus armeniaca.

#### Control group

Intervention: Participants in the control group will receive XYG (National Drug Approval Number: Z62020014; 4 g/sachet) and a matching placebo for XFOL (10 mL/bottle). Both the active drug and placebo are identical in appearance, taste, and odor. For ages 3–5 years, 1 sachet (4 g) of XYG (or placebo), administered orally 3 times daily; for ages 6–14 years, 2 sachets (8 g) of XYG (or placebo), administered orally 2–3 times daily. The color, smell and taste of the placebo for XFOL drug are consistent with those of XFOL.

XYG ingredients: Honeysuckle, Belamcanda rhizome, Tinospora pubescens root, Platycodon grandiflorus root, Scrophularia ningpoensis root, Ophiopogon japonicus root, Artificial Bovis Calculus, Borneol.

#### Treatment course

The treatment duration is 5 days (±1 day) as this period covers the critical progression phase of the disease. Participants will return for follow-up visits after completing the course to return unused medications and logcards. A post-treatment telephone follow-up will be conducted 24 h after discontinuation to assess body temperature, concomitant medications, and adverse events.

#### Rescue therapy

Acetaminophen oral suspension (brand name: Tylenol; 100 mL:3.2 g) will be administered as antipyretic rescue medication for participants with axillary temperature ≥38.2°C (Liu and Gu, 2017). For dosage, 1–3 years (12–15 kg): 3 mL per dose; 4–6 years (16–21 kg): 5 mL per dose; 7–9 years (22–27 kg): 8 mL per dose; 10–12 years (28–32 kg): 10 mL per dose. For frequency, repeat every 4–6 h if fever persists, with a maximum of 4 doses within 24 h. Persistent high fever unresponsive to rescue therapy requires immediate medical intervention.

During the trial, the use of antibiotics, antiviral agents, or other TCM with purported effectiveness for pediatric acute pharyngitis/tonsillitis is strictly prohibited. Additionally, non-protocol treatments such as infrared therapy, cupping, and acupuncture are disallowed throughout the study and follow-up periods. Acetaminophen is permitted for fever management (axillary temperature ≥38.2°C), and its dosage must adhere to the product instructions. All concomitant medications, including rescue therapies, must be meticulously documented in the CRF and original medical records, specifying the generic drug names, dosages, administration times, and reasons for use to ensure comprehensive data integrity and protocol adherence.

### Outcome measures

#### Pain measurement

The Wong-Baker Faces Pain Rating Scale (WBS) employs six facial expressions (0–10 scale) to quantify throat pain intensity (Figure 2). Children aged ≥3 years select the face best representing their current pain, with 0 indicating no pain (smiling face) and 10 reflecting severe pain (crying face) (Garra et al., 2010).

**FIGURE 2 F2:**
[figure not shown]
Faces Pain Scale for assessing throat pain in children.

#### TCM symptom evaluation

The following table outlines the grading and quantification criteria for TCM syndrome symptoms, including primary symptoms (e.g., sore throat), secondary symptoms (e.g., dry throat, fever, cough), and physical signs (e.g., pharyngeal and tonsillar findings). Symptoms are scored on a severity scale (0–6 points for primary symptoms; 0–6 points for secondary symptoms and physical signs), with higher scores indicating greater severity. Tongue and pulse characteristics are recorded but not scored (Chinese Association of Traditional Chinese Medicine, 2020) (detailed in Table 2).

**TABLE 2 T2:** Grading and quantification criteria for TCM syndrome symptoms.

Primary symptoms	Normal (0 points)	Mild (2 points)	Moderate (4 points)	Severe (6 points)
Sore throat (pain on swallowing)	None	Mild pain during swallowing	Pain during swallowing	Severe pain with difficulty swallowing

Secondary symptoms	Normal (0 points)	Mild (2 points)	Moderate (4 points)	Severe (6 points)
Dry throat	None	Mild discomfort	Dryness with burning or mild pain	Severe burning or pain
Fever	Axillary temperature ≤37.2°C in past 24 h	Axillary temperature 37.3°C–37.9°C	Axillary temperature 38°C–38.5°C	Axillary temperature >38.5°C
Cough with yellow sputum	None	Occasional cough, small amount of sticky yellow sputum	Intermittent cough, does not affect rest or sleep, sticky yellow sputum, easy to expectorate	Frequent cough affecting rest or sleep, sticky yellow sputum, difficult to expectorate

Physical signs	Normal (0 points)	Mild (2 points)	Moderate (4 points)	Severe (6 points)
Pharynx	None	Hyperemia of posterior pharyngeal wall	Hyperemia and edema of posterior pharyngeal wall	Significant hyperemia and edema of posterior pharyngeal wall, uvula, and lateral bands, with secretions
Tonsils	None	Tonsillar hyperemia	Tonsillar hyperemia and edema, with secretions or purulent spots	Tonsillar hyperemia and edema, with abundant secretions or purulent coating
Lymphadenopathy	None	Submandibular or cervical lymph nodes <1 cm, mild tenderness	Submandibular or cervical lymph nodes 1–2 cm, significant tenderness	Submandibular or cervical lymph nodes >2 cm, severe tenderness
Tongue and pulse	Tongue and pulse characteristics: recorded but not scored			

#### Baseline data

Prior to treatment initiation, comprehensive baseline data will be collected, including demographic characteristics (sex, age, height, weight, ethnicity), medical history (disease duration, past medical conditions, allergies, pre-trial medications), and diagnostic indicators (symptoms such as sore throat and fever, physical signs including pharyngeal/tonsillar erythema, and laboratory results).

#### Primary outcomes

The primary effectiveness endpoint is the throat pain resolution rate and overall effective rate at Day 5, assessed using the WBS score. Participants will record pain severity daily in logcards, with scores ranging from 0 (no pain) to 10 (severe pain). Effectiveness is defined as a ≥50% reduction in WBS score from baseline, while resolution requires a score of 0. The trial will be considered successful only if non-inferiority is demonstrated for both primary endpoints simultaneously, with the test treatment non-inferior to the control treatment.

